### Sample size calculation

The primary analysis will consist of two baseline adjusted comparisons of PR prevalence after twelve months, each comparing one of both intervention groups with the control group.

A Bonferroni adjustment for testing two times will be applied, yielding a significance level of α = 0.05/2 = 0.025. The unit of observation in the primary analysis is the home (= cluster).

It is assumed that prevalence throughout the homes will be approximately normal distributed. The estimation of the required sample size is based on the *t*-test comparing the prevalence differences between two groups (intervention and control) from baseline to twelve months. The power of each test in the primary analysis is estimated separately under the same circumstances.

Based on data of the initial study [1], a sample size of 38 homes per group is needed to detect a difference in prevalence of 5 % after twelve months with 90 % power (β = 0.10) using a two-sided significance level of 2.5 % (α = 0.025) and assuming a standard deviation of σ = 6.0 in both groups. Furthermore, presuming a dropout rate of 5 %, a sample size of 40 clusters per group, i.e. a total of 120 clusters, with a mean cluster size of 90 residents is planned.

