Data will be described at all three measurement points (T_0_, T_1_, T_2_), stratified by treatment groups using frequency tables, means, standard deviations, percentiles and prevalence, depending on the distribution of the variables. Data on the residents will be described according to the resident level. Variances and confidence intervals of the outcomes of residents will be estimated cluster-adjusted using the intra-class correlation coefficient (ICCC) [37]. In a further secondary analysis, the time courses of the prevalence in the three groups will be investigated on resident level, adjusting for clusters and for repeated measurement. A generalized linear mixed model is fitted with binary dependent variable “application of PR”. Fixed effects are treatment group, time, interaction of treatment and time, and the baseline value of PR. Cluster is a random effect, in a secondary model the interaction cluster*time is also included as a further random effect. Adjustment for repeated measurement is performed by covariance patterns [38], primarily assuming a compound symmetry structure. Other covariance structures and possible exclusion of the interaction between treatment and time will be discussed comparing different models.

Secondary outcomes (quality of life on a 10 %-subpopulation; falls and fall-related fractures) will be described at each time documented, and stratified by treatment groups. Variances and confidence intervals are cluster-adjusted using ICCC [37]. Statistical comparisons between the treatment groups will be performed using (generalized) linear mixed models as described above for the primary outcome adjusting for the clusters and the repeated measurements.

Missing values on cluster level would only occur in the case of dropout homes, which, it is assumed, will be very rare and improbable. It is assumed that the documentation of PR at each investigation time will be nearly complete, so that there is no relevant selection bias from the estimated prevalence of PR of each home. Furthermore, in the secondary analyses the mixed models use all the available values of the residents and do not exclude residents because of partially incomplete values. It is not planned to impute missing values. The level of significance is 5 %, if not stated otherwise (e.g. in the primary analysis). All of the tests are performed two-sided.

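### The lead resident-level mixed model has only a random home intercept, so its treatment-by-time test is anti-conservative if homes change differently over time; the cluster-by-time model should lead

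*Protocol article*

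**What the plan says.** The protocol article plans two layers of PR analysis under Statistical analysis. The primary one is a linear model of twelve-month home prevalence on baseline home prevalence and two group indicators, with homes as the observations. A secondary one is a resident-level mixed model for binary PR. Its fixed effects are group, time, group-by-time and baseline PR. Residents' repeated values are handled by covariance patterns, with compound symmetry first.

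For the home level of that second model the article says: "Cluster is a random effect, in a secondary model the interaction cluster*time is also included as a further random effect". So the intercept-only model leads and the cluster-by-time model comes second. On the time course it adds that "possible exclusion of the interaction between treatment and time will be discussed comparing different models". Quality of life, falls and fall-related fractures are then compared with "generalized) linear mixed models as described above for the primary outcome adjusting for the clusters and the repeated measurements", at a 5% level.

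Under Sample size calculation, the trial is sized with a *t*-test "comparing the prevalence differences between two groups (intervention and control) from baseline to twelve months", "assuming a standard deviation of σ = 6.0 in both groups". No intra-class correlation (ICC), within-resident correlation or cluster-by-time variance is given.

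**The concern.** Whole homes are randomised, so a difference between arms in change over time must be judged against how much homes vary in their change. A random intercept does not carry that variation: it is the same at every visit and drops out of any within-home difference. What remains is resident-level noise, which becomes small with about 90 residents per home. A covariance pattern on each resident's repeated values does not replace the missing home-level term, because it describes residents and not a shift shared by a whole home.

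The article itself gives reason to expect such shifts. The Background attributes PR use to each home's culture of care, and Table 2 tracks structural changes and staff fluctuation by home at T1 and T2.

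At stake are the treatment-by-time test for PR, the same test for falls and fractures where these are modelled at repeated times, and the decision to keep or drop the interaction. Falls and fractures are the safety evidence for reducing restraints, so intervals that are too narrow matter there.

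**Working it through.** **1. The plan's own figure.** Inputs (Sample size calculation): difference 5 points, σ = 6.0, two-sided α = 0.025, power 90%. Normal approximation: n = 2(2.241 + 1.282)² × 36/25 = 35.7, so 36 per group. With the noncentral *t*, power is 0.8997 at 37 and 0.908 at 38, so 38 is the first n to reach 90%. Then 38/0.95 = 40. The stated figures reproduce and are not in question.

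**2. Does σ = 6.0 imply cluster-by-time variance?** Further inputs: 90 residents per home (Sample size calculation) and prevalence about 25% (Background). In points squared, resident sampling variance of a home's T0–T2 change is 2 × 25 × 75/90 × (1 − r) = 41.7(1 − r), where r is the assumed correlation between a resident's two values. The planning variance is 6.0² = 36. Home-level change variance is needed to reach 36 once r exceeds 1 − 36/41.7 = 0.14. If an assumed ICC of 0.10 is first taken out of the resident variance, the expression is 37.5(1 − r) and the threshold is 0.04. At 30% prevalence with ICC 0.05–0.10 the threshold is about 0.15–0.20.

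**3. Reading A: T0 is a response.** The intercept-only model counts only the resident part. SE ratio = √(resident variance/36); true level = 2[1 − Φ(1.96 × ratio)].

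| Assumed r | Resident SD | SE ratio | True level, closed cohort | True level, 70% overlap |
|---|---|---|---|---|
| 0.3 | 5.40 | 0.90 | 7.8% | 6.1% |
| 0.5 | 4.56 | 0.76 | 13.6% | 8.9% |
| 0.7 | 3.54 | 0.59 | 24.8% | 13.2% |

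The last column replaces r by 0.7r. New admissions are included (Resident level criteria), so the residents seen at T0 and T2 are not all the same people; the 70% is an assumption. With ICC 0.10 taken out, the closed-cohort levels are 9.4%, 15.7% and 27.3%.

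Simulation check: logistic random-intercept model, 40 against 40 homes, 90 residents, three times, no treatment effect, 600 runs per setting. CAC is the correlation of a home's effect between times.

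| Latent ICC | CAC 1.0 | 0.95 | 0.90 | 0.80 |
|---|---|---|---|---|
| 0.10 | 5.5% | 8.7% | 13.2% | 20.0% |
| 0.05 | 3.3% | 7.0% | 7.2% | 11.7% |

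At ICC 0.10 the model SE stayed near 0.08, while the true SD of the estimate was 0.081 at CAC 1.0, 0.104 at 0.90 and 0.121 at 0.80.

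For the 10% quality-of-life subsample (about 9 residents per home), the same approach gives 5–10% for ICC up to 0.10 and CAC of 0.80 or more.

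**4. Reading B: baseline PR is a covariate, T1 and T2 are the responses.** σ = 6.0 refers to T0–T2 change and does not size this case, so these figures are illustrative. Let V be the home variance at each visit, c the share of it common to T1 and T2, and r = 0.5. Resident variance of a home's prevalence is 25 × 75/90 = 20.8 per visit. V is taken as 36, or as 36 − 20.8 = 15.2 if 36 is the total.

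- Treatment-by-time: the model counts 2 × 20.8 × 0.5 = 20.8; the truth is 20.8 + 2V(1 − c).
- Twelve-month effect: the model counts V(1 + c)/2 + 20.8; the truth is V + 20.8.
- Averaged effect: the fitted intercept variance absorbs V(1 + c)/2, which is the true home part, so the level stays near 5%.

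| V | c | Treatment-by-time | Twelve-month effect |
|---|---|---|---|
| 36 | 0 / 0.5 / 0.8 | 35% / 24% / 13% | 10.5% / 7.2% / 5.8% |
| 15.2 | 0 / 0.5 / 0.8 | 21% / 14% / 8.5% | 8.2% / 6.4% / 5.5% |

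On this reading quality of life, measured at T0 and T2 only, has a single response time. There is no treatment-by-time term, and the home intercept is the right error term.

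**The case against.** The strongest reply has four parts.

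- **The model as written points to reading B.** Baseline PR is listed as a fixed effect, so T0 is naturally a covariate. The averaged effect is then valid and the interaction asks only whether the effect differs between months 6 and 12. This stands, and it narrows the point mainly to the interaction. It does not remove it, because that interaction is the term the article proposes to keep or drop.
- **The better model is already planned.** Both fits would be available. This also stands: the fault is one of order. But the article names a lead model and gives no rule for when the two disagree.
- **The size is assumed.** Within-resident correlation, ICC, CAC and overlap are not in the article, and turnover pulls the figures down. This stands, so only ranges are given.
- **No test is named for dropping the interaction.** Correct. A test that is too liberal would tend to retain the term, so no particular wrong decision can be predicted.

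A reader might infer that the trial's main result is at risk, that spurious quality-of-life effects are likely, or that a true level of about 25% is the expected case. The article does not support these. The primary test uses homes as observations. Quality of life is unaffected on reading B and only mildly affected on reading A. On reading A, 25% needs a closed cohort with r = 0.7; on reading B, the higher treatment-by-time figures rest on assumed home variances that the article does not give. Small-sample degrees of freedom may be left to the analysis plan and are not part of this point.

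**Conclusion.** The point holds for the secondary resident-level analysis. As written, the lead model's treatment-by-time test for PR, and for falls and fractures at repeated times, is anti-conservative whenever homes differ in their change. The planning SD of 6.0 implies such differences unless residents' repeated values are nearly uncorrelated.

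With T0 as a response, a nominal 5% test runs at roughly 6–14% for assumed correlations of 0.3–0.5, with the lower end reflecting turnover; at 0.7 it is about 13–25%. With baseline as a covariate, the averaged effect stays near 5%, the twelve-month effect lies at about 5–11%, and treatment-by-time at about 8–35% under the illustrative variances. With no cluster-by-time variance there is no inflation.

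The primary cluster-level analysis, its 2.5% levels and the 40 homes per group are unaffected. Severity is moderate to minor.

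**What to change.** Exchange the two planned models. Let the model with the cluster-by-time random effect lead for PR and for secondary outcomes with repeated follow-up times, and label the intercept-only model a sensitivity analysis. Base any decision about the treatment-by-time term on the cluster-by-time model. State also whether T0 is a response or only a covariate, since the set of affected estimates depends on it.

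The cost is a change of wording and slightly wider intervals in secondary analyses. No new data are needed, and the sample size and primary analysis stay as they are.

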### Statistical analysis

Statistical analysis will follow the Good Clinical Practice (GCP) standards and will be conducted after the end of the follow-up by the blinded biostatistician (BH) in charge. Data analysis will be performed by intention to treat. In the primary analysis, the prevalence of restraints on both intervention groups will be compared to the control group on cluster level.

It is assumed that prevalence throughout the nursing homes will be approximately normal distributed.

The statistical tests will be adjusted for baseline prevalence by fitting a linear model with twelve-month prevalence of the clusters as the dependent variable and using baseline prevalence and two indicator variables of the intervention groups as the independent variables. Differences of prevalence changes between each intervention group and the control group will be estimated and statistically tested using contrasts of the model. Both tests will be performed using a two-sided level of significance of α = 2.5 %, which is adjusted for double testing by Bonferroni. Cluster adjustment will be ensured by using clusters as observation units. Based on the same linear model, a secondary analysis will estimate the contrast between the prevalence differences of both intervention groups. This result will be interpreted in a descriptive manner. A non-significant difference cannot be interpreted as the equivalence of both interventions. Possible equivalence tests do not reach enough power to get reasonable results.

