### Ethical and legal considerations

The study protocol has been approved by the ethical committees of the Universities of Lübeck in January 2015 (no. 14–251) and Halle (Saale) in March 2015 (no. 2015–02). Written informed consent will be obtained from the managers of each participating nursing home before the start of the trial. Participating nursing homes may withdraw their consent at any time. As has been successfully carried out in previous trials [1, 5, 44, 45], no written informed consent from residents or their legal guardians will be required, as the investigators will have no direct access to the residents' data.

According to data protection regulations, a member of the nursing staff will accompany the investigators. Residents’ rooms will only be entered after the nurse has asked the resident if he or she agrees to be visited. Assessment of residents’ cognition, behaviour and quality of life will be performed by nurses’ proxy rating.

All resident-related data will be pseudonymised for the investigators by using a resident code number. Only the study coordinators at the nursing homes will have access to the names of the participating residents. All electronic data and CRFs will be archived securely for ten years at the University of Lübeck and will then be destroyed. The archive will not contain the residents’ names. Due to the results of our previous trial [1], we do not expect any risks for the participating residents. Good Clinical Practice will be fully guaranteed. Hence, a random sample of nursing homes will be visited and an external data auditor will personally check the data. Research assistants will be educated about correct data collection, data processing and data protection.

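### The primary analysis uses only homes with a twelve-month value and leaves their six-month value unused; arm-related withdrawal that tracks progress could bias the contrast, modestly at the planned 5 % loss

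*Protocol article*

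**What the plan says.** The protocol article, section Statistical analysis, defines the primary model at home level. Twelve-month prevalence is the dependent variable; baseline prevalence and two arm indicators are the independent variables. On testing: "Both tests will be performed using a two-sided level of significance of α = 2.5 %, which is adjusted for double testing by Bonferroni". On the analysis population: "Data analysis will be performed by intention to treat".

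On missing data, the same section attributes missing home values to homes that drop out, "which, it is assumed, will be very rare and improbable", and then states: "It is not planned to impute missing values".

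Three other places bear on this:
- Sample size calculation: 38 homes per group are required "to detect a difference in prevalence of 5 % after twelve months with 90 % power". The text goes on: "Furthermore, presuming a dropout rate of" 5 %, which leads to 40 per group.
- Ethical and legal considerations: "Participating nursing homes may withdraw their consent at any time".
- Outcome measures: restraint use is observed at T0, at six months (T1) and at twelve months (T2).

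**The concern.** The stated model and the no-imputation rule together settle what happens to a home without T2: it cannot enter the primary analysis. This is a complete-case analysis of homes. The home's T0 value, and its T1 value if it stayed that long, are discarded. The reason given is that loss of homes is improbable, which sits badly with the article's own 5 % allowance (6 of 120 homes).

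The two intervention arms carry training and key-nurse support that the control arm does not (Table 1), nursing staff cannot be blinded (Discussion), and home managers give the consent. Withdrawal that differs by arm and is related to slow progress is therefore conceivable. If intervention homes that are not reducing restraints leave more often, the homes that remain overstate the reduction.

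**Working it through.** **1. The plan's own figures.** Inputs from Sample size calculation: difference 5 points, SD 6.0, two-sided alpha 0.025, power 0.90. The normal approximation gives 2 × 6² × (2.241 + 1.282)² / 5² = 35.7, so 36. The noncentral t gives 37.03, so 38 per group, with power 0.908. Then 38 / 0.95 = 40. Both stated figures reproduce, and 5 % means 2 of 40 homes per arm.

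**2. When bias arises.** The model adjusts for baseline. In a simulation with 2 of 40 homes lost in one arm according to T0 prevalence, the bias was 0.00; at 8 of 40 it was also 0.00. Bias requires loss linked to the course after baseline and differing between arms.

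**3. Size when loss follows the T1 change.** Assumptions not in the documents: T1-T2 correlation of change ρ = 0.6, loss in one intervention arm only, no true effect. Negative bias favours the intervention. For k homes lost of 40:
- Lost at random from the less favourable half at T1. The mean of that half lies 0.798 SD above the arm mean, so bias = −k × 6 × 0.798 × ρ / (40 − k). For k = 2: −2 × 2.87 / 38 = −0.15.
- The k worst homes at T1 leave. Bias = ρ × truncated-normal shift, which is −0.65, −1.17 and −1.65 for k = 2, 4 and 6. For k = 2: 0.6 × (−0.65) = −0.39.

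| Homes lost of 40, one arm | Worse half: formula (simulated) | Worst homes: formula (simulated) |
|---|---|---|
| 2 (5 %) | −0.15 (−0.14) | −0.39 (−0.38) |
| 4 (10 %) | −0.32 (−0.31) | −0.70 (−0.68) |
| 6 (15 %) | −0.51 (−0.50) | −0.99 (−0.96) |

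Both formulas are proportional to ρ. At 5 % loss the range is 0.15 to 0.39 for ρ = 0.6, 0.18 to 0.46 for ρ = 0.7, and at most 0.65 if the two homes with the worst T2 change leave (ρ = 1).

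**4. Effect on the test.** The standard error with 38 against 40 homes is 6 × √(1/38 + 1/40) = 1.36. The error is the chance of exceeding ±2.241 when the statistic is shifted by bias / 1.36.
- Bias 0.14: 2.6 %.
- Bias 0.38: 3.1 %.
- Bias 0.65: 4.2 %.
- Bias 0.96, with the matching 34 against 40 homes: 6.0 %.

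The nominal level is 2.5 %.

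**5. What T1 recovers.** A likelihood-type analysis that also uses T1 (ρ = 0.7, dropout probability rising with the score) gives at 5 % loss:
- loss driven by T1: −0.18 without T1, 0.03 with it;
- loss driven by T2: −0.29 without T1, −0.16 with it.

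In the second case the share of bias that remains is about 1 − ρ²: 0.51 for ρ = 0.7 and 0.64 for ρ = 0.6.

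**The case against.** The strongest reply is that little is at stake and that the plan is not blind to the problem. At the planned loss the bias is 3 to 8 % of the target (0.14 / 5 and 0.38 / 5), well below one standard error. The secondary generalized linear mixed model uses all available resident values, so T1 data of homes that leave later do enter a planned analysis. Table 2 schedules a structured record of reasons for drop-out from T0 to T2, and reporting will follow the CONSORT extension for cluster trials. Sensitivity analyses for missing clusters commonly sit in a statistical analysis plan, which is not shown.

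Most of this stands. It rules out two stronger readings:
- A reader might infer that nothing planned would reveal selective withdrawal. The mixed model and the drop-out documentation show otherwise. The mixed model is no substitute, however: it works at resident level on a binary outcome and is not the confirmatory home-level contrast.
- A reader might infer that the intention-to-treat statement is false. It can equally mean analysis by randomised arm, and it does not claim that missing outcomes are filled in.

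The appeal to an unseen analysis plan does not dispose of the point. The article does not leave missing homes open; it states the rule and the reason for it.

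A further fair objection concerns the remedy. Simulating loss from T1 guarantees that a model with T1 looks unbiased. Table 2 places the educational sessions at T0 and logs supervision over the first three months, so a home that leaves because of that burden has no T1 value to use.

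**Conclusion.** The point holds as a modest weakness that is cheap to remove. The primary analysis is confined to homes with T2, ignores T1, and rests on a dropout assumption that does not match the planned 5 %. The contrast can be biased if withdrawal differs by arm and tracks progress at six months. The size is about 0.1 to 0.4 points at 5 % loss, with a per-test error of about 2.6 to 3.1 %. It reaches 0.5 to 1.0 point only at roughly 10 to 15 % loss concentrated in one arm.

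These figures rest on ρ = 0.6, one-sided loss and selection on the T1 change, none of which the documents supply. A reader might infer that the trial's result will be biased. The documents do not support that: nothing in them shows withdrawal related to progress, and withdrawal depending on arm and baseline alone leaves the estimate unbiased.

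**What to change.** 1. Keep the T2 contrast at two-sided 2.5 % as primary, but estimate it in a home-level repeated-measures model of T1 and T2 with baseline-by-time, group-by-time and an unstructured 2×2 covariance. If no home is missing, the T2 estimate equals that of the stated linear model. If a home leaves after six months, its T1 value contributes.
2. Add one delta-type sensitivity analysis with all 120 randomised homes. Impute missing T2 prevalence from T0, T1 where available, and arm; then shift the imputed values by a range of amounts, separately by arm. With 2 of 40 homes missing, a shift of δ moves the arm mean by 2/40 × δ, so 10 points move it by 0.5. This covers homes that leave before T1 and withdrawal that depends on T2, which step 1 cannot. Carrying the last value forward would not do, because it assumes no further change. State whether data collected before consent is withdrawn may be used; both steps presume so.
3. Replace the statement that loss of homes is improbable with the planned 5 %.

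The cost is a slightly longer model description and a little programming. T1 is already scheduled, and neither the sample size nor alpha changes.

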### Health economic evaluation

The objective of the economic evaluation is to estimate the cost-effectiveness of the intervention in terms of additional costs per additional resident who is not being physically restrained. The economic evaluation will be performed from the perspective of the German social insurance (statutory health insurance and long-term care insurance). The incremental cost-effectiveness ratio (ICER) will be calculated, i.e. the ratio of the difference in costs between intervention and control groups divided by the difference in the proportion of residents without physical restraints. Effect parameters of the clinical trial will be used. During the study, cost parameters will be collected on intervention-related components as well as on outcome-related components. Cost parameters will be registered throughout the course of the study and during process evaluation. Resource use will be quantified, using a standardised protocol which is based on previously used protocols [1, 36]. Resource use and costs directly associated with the intervention will be derived from the study documentation. Costs explicitly associated with developing the information and training material, and conducting the study, such as the data collection, will not be taken into account.

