Focus groups will be analysed by content analysis [39]. Two independent research team members will identify initial themes describing comparable aspects or meanings. To abstract the content, all initial themes will be labelled with codes. Based on the codes, categories and sub-categories will be developed. Coding and analysis will be discussed constantly. Disagreements about the themes will be resolved in a discussion. The content will be summarised and narratively described.

For the health economics analysis, mean costs as well as cost differences between intervention and control groups will be calculated. Cluster-adjustment will be conducted. Sampling uncertainty (95 % confidence intervals) will be estimated using bootstrap procedure because cost data are usually skewed. Effects will be taken from the documented events. ICER will be estimated in terms of costs per resident with avoided PR. The non-parametric bootstrap method will be employed to generate confidence intervals around the ICER estimate derived from the study sample [40, 41]. Uncertainty surrounding the ICER will also be presented on the cost-effectiveness plane and as the cost-effectiveness acceptability curve [42, 43]. Besides statistical uncertainty (sampling variation) with regard to costs and effects, every economic evaluation may contain some degree of data imprecision (e.g. resource costs/prices), which should be accounted for. To handle this type of uncertainty, a sensitivity analysis will be employed. In the sensitivity analysis, (uncertain) parameter(s) of the base-case analysis will be varied to determine whether changes in these parameters influence the results. We will report both, the revised point estimates and revised confidence intervals for costs, effectiveness, and cost- effectiveness that result from the sensitivity analyses.

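### The bootstrap confidence interval promised for the ICER has no condition on the effect in its denominator, and it becomes uninterpretable if a programme's effect is well below the planned 5 points

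*Protocol article*

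**What the plan says.** The Health economic evaluation section defines the ICER as the "difference in costs between intervention and control groups divided by the difference in the proportion of residents without physical restraints". The last paragraph of the Statistical analysis section sets out how its uncertainty is handled:

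- For costs: "Sampling uncertainty (95 % confidence intervals) will be estimated using bootstrap procedure because cost data are usually skewed".
- For the ratio: "The non-parametric bootstrap method will be employed to generate confidence intervals around the ICER estimate derived from the study sample".
- In addition: "Uncertainty surrounding the ICER will also be presented on the cost-effectiveness plane and as the cost-effectiveness acceptability curve".
- For uncertain parameters, the authors will report "revised point estimates and revised confidence intervals for costs, effectiveness, and cost- effectiveness that result from the sensitivity analyses".

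No sentence makes the interval for the ratio depend on the size or clarity of the effect difference, and none says what is reported if replicates spread over several quadrants of the plane.

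**The concern.** The sign of a ratio does not identify a quadrant of the cost-effectiveness plane. A positive ICER arises when a programme costs more and works, and also when it saves money and works less well. A negative ICER arises when the programme dominates control and also when it is dominated. While nearly all replicates lie on one side of zero effect this does no harm. Once they straddle zero, the ratios jump from very large positive to very large negative values as the effect passes through zero. Dominated replicates then land at the low end, where a reader looks for savings.

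At stake is one published summary for each programme, repeated in the sensitivity analyses. The Discussion raises the possibility that the concise programme is more cost-effective, and the Dissemination policy says that policy makers will be informed. Readers there may take the two limits of an interval at face value.

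**Working it through.** **Inputs.** From the Sample size calculation section: a difference of 5 percentage points, SD 6.0 (read as percentage points at home level), two-sided α of 0.025 per comparison, 90% power, 38 homes per group, 5% dropout, 40 per group planned. From the Statistical analysis section: 95% intervals in the economic analysis. The document gives no cost figures.

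**The plan's own figure.** With the noncentral t distribution, 37 homes per group give power 0.8997 and 38 give 0.908, so 38 is the smallest number that reaches 90%. Then 38/0.95 = 40. The stated sample size reproduces.

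**Precision of the denominator.** SE = 6.0 × √(2/40) = 1.34 points.

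**Chance of straddling zero.** A 95% percentile interval for the effect includes zero when at least 2.5% of replicates lie on each side of zero. For a true effect d, the chance of this is approximately Φ(1.96 − d/SE) − Φ(−1.96 − d/SE). The share of the sampling distribution at or below zero is Φ(−d/SE).

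| True effect (points) | d/SE | Share at or below 0 | Chance that the 95% interval includes 0 |
|---|---|---|---|
| 5 | 3.73 | 0.01% | 4% |
| 4 | 2.98 | 0.14% | 15% |
| 3 | 2.24 | 1.3% | 39% |
| 2 | 1.49 | 6.8% | 68% |
| 1 | 0.75 | 23% | 88% |
| 0 | 0 | 50% | 95% |

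With 38 homes per group the SE is 1.38, and the last column is 5% at 5 points, 41% at 3 and 69% at 2.

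**What the ratio interval looks like.** This needs assumed costs, so it is illustrative only. Take a cost difference of 50 units and a home-level cost SD of 100, independent of effect, so that the SE of the cost difference is 100 × √(2/40) = 22.4. Draw cost and effect differences from normal distributions centred on the true values, and take the 2.5th and 97.5th percentiles of the ratio:

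- At 5 points they are about 120 and 2,640, which is readable.
- At 2 points they are about −16,000 and +22,700. The lower limit looks like a large saving, yet only about 1.3% of draws save money. Almost all the negative ratios come from draws that cost more and work less well (6.75% of all draws).

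**Coverage.** A simulation with the same assumed costs (600 trials, 1,000 percentile-bootstrap replicates each, 40 homes per arm) gave coverage of the true ratio between 0.965 and 0.98 at effects of 1, 2, 3 and 5 points, and 0.895 at 0.5 points. The median interval width was about 2,400 units at 5 points, 7,900 at 3, 33,000 at 2 and 70,000 at 1. At exactly zero effect the true ratio is undefined.

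**The case against.** The strongest reply is that quadrant-safe displays are already promised. The plane shows where the replicates fall. The acceptability curve gives, at each willingness to pay, the share of replicates with positive net benefit. Separate intervals for costs and effectiveness are planned as well, so a careful reader would notice an effect interval that includes zero. This stands, and it keeps the point small. But the plane and curve are added to the ratio interval and do not replace it, so the interval would still be reported.

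A second reply is that the article does not say how the limits are formed, and such detail may sit in a fuller plan or in the cited methods literature. That is fair as to detail. The point does not rest on a missing algorithm. It rests on a stated commitment to an interval for the ratio, made without condition and repeated for the sensitivity analyses.

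Some stronger readings are tempting, and the document does not support them:

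- A reader might infer that the interval is invalid in the sense of coverage. Under the assumed costs, coverage was adequate from 1 to 5 points and fell short only very near zero. What is lost is meaning.
- A reader might infer trouble at the planned effect if homes vary more than assumed, for example in an unadjusted comparison at twelve months. No larger SD is given, the Health economic evaluation section says that the trial's effect parameters will be used, and the trial's estimate is adjusted for baseline.
- A reader might infer that a programme could be rolled out on this interval after a null result. The Discussion makes its roll-out statement conditional on success. The effectiveness test is at two-sided 2.5%, so a programme that passes has an estimate of about 2.24 standard errors or more. If the same estimate enters the ICER, its 95% effect interval excludes zero and the difficulty essentially does not arise.

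**Conclusion.** The concern holds as a minor point about one secondary summary. The unconditional ICER interval behaves well at the planned 5 points, where the effect interval includes zero about 4% of the time. It often becomes unreadable when a programme's true effect is clearly smaller: about 39% of the time at 3 points and 68% at 2. The primary test, the sample size and the effectiveness conclusion are untouched.

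The percentages assume that 6.0 is in percentage points, that it applies to the effect estimate used in the ICER, that 40 homes per arm are analysed and that the estimate is approximately normal. The illustrative interval limits, widths and coverage also depend on assumed costs, but the percentages do not.

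**What to change.** In the health economics paragraph, make incremental net benefit the quantity that carries the confidence interval: willingness to pay per additional unrestrained resident × effect difference − cost difference. Give a 95% interval over a stated range of willingness to pay, from the same cluster-adjusted bootstrap replicates. Then add a rule such as: *A confidence interval for the ICER will be given only if at least 97.5% of bootstrap replicates have an effect difference of the same sign; otherwise the point estimate, the cost-effectiveness plane and the acceptability curve will be given. The same rule applies in the sensitivity analyses.*

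This costs wording only: the replicates are already needed for the plane and the curve, and no data collection or sample size changes. There are two small downsides. A willingness-to-pay range has to be stated, and a programme with little effect may be published without an ICER interval.
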